3.8 Outcomes and definitions

1. PaO2: Partial pressure of oxygen in post-ductal arterial blood
2. A-a DO2 : calculated by PAO2 - PaO2

where PAO2 = [FiO2 x (PB - 47)] - PaCO2

PB= ambient barometric pressure in mm Hg

1. A/a O2 : calculated by PAO2 / PaO2

where PAO2 = [FiO2 x (PB - 47)] - PaCO2

1. SpO2: Oxygen saturation by pulse oximetry (pre-ductal)

3.9 Statistical issues

The power of the study is 85% with n=20 in each group, =0.05, assuming we need to detect a difference of 25 % with a standard deviation at 25% of the mean. Repeated measures ANOVA or unpaired t-test will be used if data are normally distributed, otherwise non-parametric tests will be used. Data will be analyzed by intention to treat. Small numbers are required since this is a pilot study to show physiologic efficacy of the technique and is not meant to study clinical outcomes.

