#### Neonates with hypoxemia (PaO2 < 50 mm Hg) or respiratory acidosis while on 100% oxygen at the onset are usually intubated and mechanically ventilated. The A-a DO2 usually is > 600 mm Hg in this situation, and often more than 630 mm Hg, depending on the PaCO2. However, neonates who present with markedly elevated A-a DO2 (> 500 mm Hg) but with adequate oxygenation (PaO2 50-150 mm Hg on FiO2 > 0.95), respiratory effort, and acid-base status often present a dilemma – to intubate and mechanically ventilate or not? These neonates with either a severe V/Q mismatch (intra-pulmonary shunt) or right to left shunts (extra-pulmonary shunt) (frequently both factors are operative to a variable degree) are often maintained on high oxygen concentrations (FiO2 > 0.7) delivered by oxygen hood, in an attempt to maintain adequate oxygenation and possibly accelerate the spontaneous resolution of elevated pulmonary pressures and minimize the risk of hypoxic pulmonary vasoconstriction or V/Q mismatch without resorting to mechanical ventilation. While some of these neonates improve spontaneously, others persist with high A-a DO2 and ultimately require mechanical ventilation and occasionally ECMO. The neonates who deteriorate are often those with worse oxygenation and higher A-a DO2.

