1. Apparatus: FiO2 and NO/NO2 concentrations will be checked in the **inflow gas** at the beginning, and continuous monitoring of FiO2 and NO/NO2 concentrations in the **inner hood** will be done till exit from study. FiO2 and NO/NO2 concentrations will also be measured **outside the hood** 30 min and one hour after commencement of the treatment, at a distance of one foot (30 cm) from the front of the hood.
2. Baby: **ABGs** at 0 hours (the last ABG before beginning treatment gas) and 1 hour will be used for the study. **MetHb** will also be measured in these samples. Frequency of ABG and other lab investigations at other times will be at the discretion of the attending physician, but should be at least q 1 hour for the five hours on the study. **Oxygen saturation, heart rate, respiratory rate** and **blood pressures** (by arterial catheter) will be monitored continuously through the period of study. A **platelet count** obtained less than 12 hours before entry into the study will also be compared with one obtained immediately after completion of one hour of exposure to the treatment gas. **Echocardiograms** are encouraged before entry into the study, as echocardiograms are usually part of the clinical investigation in neonates with suspected PPHN, but are not a pre-requisite for entry in view of time and technical constraints.

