3.6 Co-interventions and contamination

Co-interventions will be minimized by randomization, since all groups should be affected approximately equally. However, note will be made of interventions that could potentially alter outcome variables, such as fluid management. The major contaminant is that neonates with elevated A-a DO2 are a heterogeneous population with variable degrees of V/Q mismatch and right to left shunting and may not respond either in the same direction or magnitude to any intervention, including the administration of NO. However, this study is a pilot study to evaluate the effect of NO administered by oxygen hood in a "real-world" situation where heterogeneity is the rule, and transition from fetal to neonatal physiology is occurring. Another possible contaminant is that the NO group will have a slightly lower FiO2 (about 95-96% rather than 97-98% in the oxygen hood, due to admixture of the nitrogen carrier gas) than the oxygen group, and this will place the NO group at a disadvantage regarding the delivered oxygen concentration. However, similar small decreases in FiO2 occur even with NO use during mechanical ventilation and this is considered acceptable practice, since the improvements in oxygenation with NO are considered to outweigh the decreases due to the small reduction in FiO2.

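### The primary 1-h PaO2 comparison is left between two tests; one ANCOVA on the 0-h PaO2 would settle it and add power at no cost

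*Protocol*

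**What the plan says.** The protocol summary makes PaO2 after one hour of treatment gas the primary outcome. For the analysis, the summary and section 3.9 carry the same sentence: "Repeated measures ANOVA or unpaired t-test will be used if data are normally distributed, otherwise non-parametric tests will be used". Neither place says which parametric test is primary. If it is the ANOVA, neither says which time points enter or which term is tested.

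The sizing in section 3.9 reads "The power of the study is 85% with n=20 in each group", "assuming we need to detect a difference of 25 % with a standard deviation at 25% of the mean", with a significance level of 0.05. Section 3.3 allocates 1:1, and section 3.9 specifies analysis by intention to treat.

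Under Monitoring, section 3.4 says that the blood gases "at 0 hours (the last ABG before beginning treatment gas) and 1 hour will be used for the study". So each infant is meant to have a pre-treatment PaO2 and a 1-h PaO2 on record. No analysis that adjusts the second for the first is named.

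**The concern.** The two named tests do not examine the same contrast. An unpaired t-test of 1-h PaO2, or its rank counterpart, compares the arms on the primary outcome but leaves out the 0-h value. A repeated measures ANOVA on 0 h and 1 h brings that value in, in one of two ways. Its group-by-time term is a t-test of the change from 0 h to 1 h. Its group main effect averages a gas taken before treatment into the comparison, which halves the expected difference.

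Two things are at stake. First, power depends on which test is run, and the plan leaves that open. Second, with 20 infants per arm, chance differences in starting PaO2 pass into an unadjusted comparison. If the 0-h SD is also 25% of the mean (an assumption), the baseline difference between arms has a standard error of 0.25 × √(2/20) = 0.079, about 8% of the mean against a target of 25%. Adjustment removes the part of that difference which predicts the 1-h value.

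**Working it through.** **Inputs.** From section 3.9: n = 20 per group, difference δ = 0.25 and SD σ = 0.25 (both as fractions of the mean), level 0.05. Two-sided testing is assumed, because sidedness is not stated. The correlation ρ between 0-h and 1-h PaO2 is not in the documents; it is set at 0, 0.3, 0.5 and 0.7, with equal SDs at both times.

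**Step 1: the plan's own figure.** For the unpaired t-test the noncentrality is δ / (σ√(2/n)) = 0.25 / (0.25 × √0.1) = 3.162. With 38 degrees of freedom the power is 86.9%. The rank test, at asymptotic relative efficiency 0.955, has 85.3%. The stated 85% is reproduced without the 0-h value.

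**Step 2: the alternatives.** Each replaces δ/σ = 1 by its own standardised effect:

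- ANCOVA: residual SD σ√(1 − ρ²), effect 1/√(1 − ρ²), 37 df.
- Group-by-time term: SD of change σ√(2(1 − ρ)), effect 1/√(2(1 − ρ)), 38 df.
- Group main effect over 0 and 1 h: difference δ/2, SD σ√((1 + ρ)/2), effect 0.5/√((1 + ρ)/2), 38 df.

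At ρ = 0.5, for example, the three effects are 1/√0.75 = 1.155, 1/√1 = 1.000 and 0.5/√0.75 = 0.577.

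| Power, n = 20 per group | ρ = 0 | 0.3 | 0.5 | 0.7 |
|---|---|---|---|---|
| Unpaired t-test | 86.9% | 86.9% | 86.9% | 86.9% |
| Group-by-time term | 58.7% | 74.0% | 86.9% | 97.8% |
| Group main effect, 0 and 1 h | 58.7% | 48.1% | 42.9% | 38.7% |
| ANCOVA on 0-h PaO2 | 86.8% | 89.8% | 94.5% | 99.1% |

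ANCOVA less the t-test is −0.1, +2.9, +7.6 and +12.2 points. The group-by-time term falls below the t-test when ρ is under 0.5, equals it at 0.5 and exceeds it above.

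**Step 3: what the SD refers to.** If σ is 25% of each arm's own mean, the SDs are 0.25 and 0.25 × 1.25 = 0.3125. The pooled SD is √((0.25² + 0.3125²)/2) = 0.283, the effect is 0.25/0.283 = 0.883, and the t-test has 77.7% power.

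**Step 4: a log scale.** With a 25% CV in both arms, the log SD is √ln(1 + 0.25²) = 0.246. A ratio of 1.25 is ln 1.25 = 0.223, so the effect is 0.223/0.246 = 0.906. ANCOVA power on that scale is about 80, 83, 90 and 97% at ρ = 0, 0.3, 0.5 and 0.7. The raw-scale figures in the table must not be quoted for a log-scale analysis.

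**Step 5: the normality check.** Simulating a Shapiro test in each arm followed by t-test or Mann-Whitney (6,000 runs per scenario; normal data, and lognormal data with CV 25% and 50%) gave a type I error of 4.7 to 5.8%. Power was within about 2 points of always using either test.

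**The case against.** The strongest reply is that nothing here is invalid. The unpaired t-test is a sound analysis of the stated primary outcome, it delivers the stated power, and preferring ANCOVA in a pilot is a matter of efficiency. Covariates and model terms are also often left to a statistical analysis plan. The first part stands, and it is why this is an improvement rather than an error. The second carries less weight, because the protocol does not leave the test open in silence. It names two tests whose power differs widely on its own inputs.

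The gain may also be small. Section 3.6 expects infants who "may not respond either in the same direction or magnitude to any intervention", and section 5.2 adds rapid spontaneous improvement. Both could lower the correlation, and near zero ANCOVA gains nothing. That stands, so the gain can only be given as a range.

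The summary's sizing sentence runs words together at the PaO2 difference, and a change symbol may have been lost in text extraction. If the sizing was on change, the 86.9% would belong to the change-score test. ANCOVA would still have a residual SD no larger than that test's. Section 3.9 and the primary outcome do not describe a change.

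Some stronger readings are tempting, but the documents do not support them:

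- A reader might infer that the normality check chooses between ANOVA and t-test, or that it damages the error rate. It chooses only between parametric and rank tests, and step 5 shows little effect.
- A reader might infer that repeated measures ANOVA ignores the baseline. Its group-by-time term uses it, and at a correlation of 0.7 comes within 1.3 points of ANCOVA.
- A reader might infer that the 25% SD is too low, because section 2.1 describes PaO2 of 50 to 150 mm Hg. That is background, not the entry criterion. At 100% oxygen, with an assumed barometric pressure of 760 and PaCO2 of 40 mm Hg, the entry window in section 3.2 gives 73 to 173 mm Hg. Spread evenly, that is a CV of (100/√12)/123 = 23.5%, within the plan. The documents give no larger SD, and do not show that baseline spread is the main source of variance at 1 h.

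**Conclusion.** The point holds as a free improvement. The protocol names two parametric tests for one primary outcome and no rule between them. The one that reproduces its power ignores a baseline value that it already collects, and the other uses that value less efficiently than ANCOVA. Over correlations from 0 to 0.7, ANCOVA is never materially below any named option. It gains 3 to 12 points on the t-test from 0.3 to 0.7 and essentially nothing at 0.

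This rests on two-sided testing, equal SDs at 0 h and 1 h, and an assumed correlation. A reader might conclude that the 85% is wrong. It is not: it stands for the unpaired t-test if the SD is 25% of a common mean, and becomes 77.7% if the SD is 25% of each arm's own mean.

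**What to change.** In section 3.9 and the summary, replace the sentence on tests with one primary analysis: ANCOVA of first-period 1-h PaO2 on randomised arm, with 0-h PaO2 as covariate, in all randomised infants. Report the adjusted difference with its 95% CI, and add a rank-based analysis as a sensitivity check in place of the normality rule. Keep repeated measures models for describing the weaning course.

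If a ratio is preferred because the target is a percentage, analyse log PaO2 with log 0-h PaO2 as covariate and state power on that scale (step 4). In either case, say which mean the 25% SD refers to and which correlation is assumed.

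The cost is wording only: no extra gases, no extra infants and no change to the conduct of the trial. The power statement becomes explicitly conditional on the SD and the correlation.

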**4. Ethical considerations**

1. Is NO safe to administer by oxyhood? : 20 ppm of NO has been safely administered during mechanical ventilation to many neonates and infants over the last few years. Administration by oxygen hood, when the concentration of inhaled NO is being continuously monitored, is probably as safe or even safer than administration during mechanical ventilation, since the additional hazards of barotrauma/volutrauma of mechanical ventilation are not superimposed.
2. Is it ethical to withdraw NO after a one hour administration at 20 ppm? : Since this is a pilot study to evaluate the physiologic efficacy of the method, and is not an evaluation of long-term NO by oxyhood on clincal outcomes, it is ethical to wean off NO to 100% oxygen by hood, which is the established practice.
3. Is it ethical to use oxygen rather than nitrogen as the control gas, since the FiO2 of the oxygen group will be higher? : Oxygen is the established and conventional method, and is known to reduce pulmonary arterial pressures. Hence it is ethical to use oxygen rather than nitrogen as the control gas.
4. If weaning from treatment gas is difficult, should treatment be continued on a long term basis? : Again, since this study is to evaluate the physiologic efficacy and not clinical outcomes, and this method of administration is still experimental, we do not favor administration of the treatment gas on a long term basis, although slower weaning can be performed.
5. If a response is seen to the treatment gas, but is not marked, should the treatment gas concentration be increased?: No, most studies have shown that neonates who respond usually do so with 20 ppm. Also, with increasing treatment gas, FiO2 decreases. When the concentration is maintained at 20 ppm or less, FiO2 is more than 95%.
6. Is it ethical to use a control group, since NO is already known to reduce pulmonary pressures and improve oxygenation in mechanically ventilated animals and neonates? : Oxygen is the established and conventional method, and the administration of NO by hood is still experimental. Also, there is provision for a crossover to the other group if the neonate still meets entry criteria after weaning from the treatment gas, so in case of no improvement, the neonate will still access both forms of therapy.
7. **Feasibility**
   1. Available population / estimated recruitment time

Every week at UAB RNICU, approximately one term neonate requires administration of 100% oxygen by hood for an elevated A-a DO2. This works out to about 50 neonates per year. Based on the assumption that consent would be available in 80%, and one fourth of the remainder (10 of 40) are excluded for various reasons, such as inability to place an arterial catheter, rapid deterioration requiring mechanical ventilation, etc, 30 neonates can be enrolled in one year. The estimated recruitment time is hence 15 months for the projected sample size of 40. In case of slow enrollment over the first 3 months, the NICU at Children’s hospital and at Cooper Green can also be used for enrollment, after IRB approval.

5.2 Potential pitfalls of study design

One problem is the heterogeneity in patient population, with a varying combination of V/Q mismatch and right to left shunting of different etiologies. The response to the treatment gas may hence differ in direction and magnitude. Another issue is that a significant proportion of neonates may also improve very rapidly, before and during entry into the study. This should hopefully be equally divided among the groups by randomization.

